## Abstract

**Background:**

Stereotactic radiosurgery (SRS) has emerged as a common adjuvant modality used with surgery for resectable brain metastases (BMs). However, the optimal sequence of the multi-modality therapy has not been established. The goal of the study is to evaluate 6-month local control utilizing pre-operative SRS followed by surgical resection for patients with 1–4 brain metastases.

**Methods:**

This prospective, single arm, phase II trial will recruit patients with up to 4 brain metastases and at least one resectable lesion. All lesions will be treated with SRS and symptomatic lesions will be resected within 1–4 days after SRS. Patients will be monitored for 6-month local control, in-brain progression free survival, distant in-brain failure, rate of leptomeningeal spread, radiation necrosis and overall survival. Additionally, we will also perform correlative radiobiological molecular studies to assess the effect of radiation dosing on the tumor tissue and clinical outcomes. We expect that pre-operative SRS to the gross tumor prior to surgical resection will improve local control and decrease leptomeningeal failure.

**Discussion:**

Our study is the second prospective trial to investigate the efficacy of pre-operative SRS in the treatment of multiple BMs. In addition, the correlative molecular studies will be the first to investigate early response of BMs at a cellular and genetic level in response to radiation doses and potentially provide molecular prognostic markers for local control and overall survival.

**Trial registration:**

Clinicaltrials.gov identifier: NCT03398694 (registration date: January 12, 2018).

## Issue Section

Research – Human – Study protocols

## Background

Incidence of brain metastases (BMs) is increasing with improved systemic therapies, many of which have a limited impact on intracranial disease. [1, 2] Historically a combination of surgical removal with subsequent whole brain radiation therapy (WBRT) was the gold standard for managing patients with a single, large BM and WBRT alone for patients with multiple metastases. [3, 4] Recent advances in the systemic treatment of various cancers have resulted in long-term survivors. [1, 2, 5] WBRT is associated with debilitating neurocognitive dysfunction, which results in significant impairment in the quality of life of long-term survivors. [6–9] As a result, current practice patterns shifted away from use of WBRT for oligo-metastasis, defined as limited number of BMs, reserving WBRT as salvage therapy or for disseminated BMs. [9, 10] Stereotactic radiosurgery (SRS) delivers high dose of radiation in a highly conformal way to relatively small target (< 3 cm) with minimal radiation to the surrounding normal tissue. [11] Since its conception, SRS emerged as a leading modality to treat BMs in variety of clinical scenarios including a boost with WBRT, as definitive treatment alone for patients with limited number of BMs and as an adjuvant treatment modality in pre- or post-operative setting. [12–14] Many tumors, regardless of whether they are radiosensitive or resistant, single or multiple, can be adequately managed with SRS. [10, 11, 15]

Although there has been no consensus on combination therapy with surgery and SRS [16, 17], surgical resection continues to play an important role in patients with a limited number of BMs and relatively good performance status where: 1) pathological diagnosis is needed, 2) a large BM (> 2 cm) causing significant mass effect necessitating direct decompression, and/or 3) neurological signs and symptoms refractory to corticosteroid management. [18, 19] Therefore, for patients with 1–4 BMs, especially in the above mentioned scenarios, adjuvant radiosurgery for surgically resected lesions is a common practice to achieve high LC. [9, 10]

Several clinical studies evaluating the role of post-operative SRS in management of BMs concluded that SRS is a safe and effective adjuvant treatment strategy for BMs (Table 2). A systematic review of 14 studies involving 629 patients treated with SRS after surgical resection showed pooled LC rate of 83%, distant intracranial failure of 49% and need for salvage WBRT in 29% of cases. [20] In addition, time to salvage therapy from initial resection was found to be 8.4 months and 10–33% of patients suffered cavity-SRS induced complications such as radiation-induced edema in 43% and radiation necrosis (RN) in 23%. [20] Two recently published phase III trials of post-operative SRS by Mahajan et al. and Brown et al. demonstrated local control efficacy and neurocognitive preservation compared with WBRT, respectively. [9, 21] Mahajan et al. prospectively randomized 132 patients in a single institution phase III study comparing observation and post-operative SRS and showed a significant improvement in local tumor recurrence-free rate at 12-month in post-operative SRS arm (72%) compared to observation arm (43%). [21] In the same journal issue, Brown et al. reported a multi-center prospective randomized phase III study to compare the post-operative SRS and WBRT in a total of 194 patients and observed similar overall survival but significantly improved neurocognition in post-operative SRS compared with WBRT. [9] Interestingly, their secondary endpoint analysis demonstrated a lower surgical bed and local control rate as compared to data previously reported. [9, 21] With a 6-month surgical bed control of 80.4% and an estimated 60.5% at 12-month, the author discussed that lower LC rate after SRS could be due to falsely elevated frequency of recurrence by including “pseudoprogression” on imaging and patients and tumor mark-up differences between trials. [9] Although there has been some discrepancy in the literature regarding to local control rates in patients receiving post-operative SRS (Table 2), these studies nevertheless support the combination use of surgery and SRS as an effective way to treat brain oligometastasis to delay WBRT and the associated neurocognitive and quality of life decline.

**Table 2 Tab2:** Published studies of Post-op SRS after Metastases Resection

Study	Treatment Modalities	Number of Patients	Median survival (months)	LR (%)	DBF (%)
Bahl, 2006 [36]	Op + SRS/fSRT	7	8.9	57.1	14.3
Kim, 2006 [37]	Op + GKRS	79	16	5.1	NA
Soltys, 2008 [22]	Op + CK	72	15.1	21	49.2
Iwai, 2008 [38]	Op + GKRS	21	20	23.8	47.6
Mathieu, 2008 [39]	Op + GKRS	40	13	27	54.1
Limbrick, 2009 [40]	Op + GKRS	15	20	20	60
Jagannathan, 2009 [41]	Op + GKRS	47	11	6.4	72.3
Robbins, 2012 [42]	Op + SRS	85	12.1	18.8	55.3
Johnson, 2016 [43]	Op + GKRS	112	12.9	15.6	NA
Brown, 2017 [9]	Op + SRS	98	12.2	19.6 (6 m)	NA
Mahajan, 2017 [21]	Op + SRS	63	17	28	58

The drawbacks for post-operative SRS include the need for cavity margin expansion, the unpredictability of patients’ postoperative course and potential delay in SRS treatment after surgery. Soltys et al. analyzed 76 post-operative SRS cases and demonstrated that increasing conformality index significantly correlated with improved LC and concluded that a 2-mm margin should be used around the resection cavity due to the possible imprecise nature of defining the target volume in a post-surgical setting. [22] Therefore, clinicians began to investigate an alternative paradigm of using preoperative SRS to reach excellent local control and preserve cognitive function.

Atalar et al. retrospectively analyzed the risk of leptomeningeal disease (LMD) in 175 patients with BMs treated with post-operative SRS and found that 13% developed LMD 5 months following SRS. [23] In Mahajan’s study, the LMD reached 28% at 12 month in post-operative SRS arm as compared to 16% in observation arm, though the difference did not reach statistical significance. It was, therefore, hypothesized that pre-resection SRS would improve the risk of LMD by sterilizing microscopic, dislodged tumor cells to prevent spread during surgery. [23, 24] In addition, another potential advantage of pre-operative SRS is a theoretical increased response to radiation due to intact vasculature and greater peri-tumoral oxygen content. [25–27] Studies have shown that lower doses of radiation are required for tumor control when the tumor has an intact blood supply and is oxygenated. This is due to radiation-induced DNA damage that ionizes oxygen molecules and generates oxygen-based free radicals which in turn damage nearby DNA resulting in tumor killing. [25, 26] In the setting of BMs, it is plausible that lower radiation doses are needed to control microscopic disease if the SRS is given prior to surgery. [26]

The first pre-operative SRS study was published by Asher et al where 47 patients were treated consecutively with neoadjuvant SRS before surgical resection, with 24 of those patients analyzed as part of a prospective trial, and the results showed 6-month and 12-month LC rate of 97.8 and 85.6% respectively (Table 3). [28] Subsequently Patel et al performed a multi-institutional retrospective comparison of outcomes and toxicities for pre-operative SRS compared to post-operative SRS for 180 patients. [29] The planning target volume (PTV) of pre-operative SRS had 0 mm margin expansion from gross tumor volume (GTV) compared to 2 mm margin for PTV of post-operative SRS. The study did not note any statistical difference in the rates of local recurrence, distant brain recurrence, and OS but the pre-operative SRS cohort demonstrated significantly lower rates of symptomatic RN (4.9% vs. 16.4%, *p* = 0.01) and LMD (3.2% vs. 16.6%, p = 0.01) than their post-operative SRS counterpart. [29] The abstract of an updated retrospective analysis of 117 patients with 125 lesions treated with pre-op SRS is now available online (https://www.redjournal.org/article/S0360-3016(18)31346-4/fulltext) and reported the 1 and 2-year cavity LC rate to be 80.1 and 74.9%, distant in-brain failure (DBF): 45.3 and 60.2%, and LMD: 4.3 and 4.3%, respectively. Nevertheless, the results were likely limited by some intrinsic selection bias, as the two retrospective cohort groups were statistically different in their baseline performance status (Figure 1).

**Table 3 Tab3:** Published studies of Pre-op SRS prior to Metastases Resection

Study	Treatment Modalities (Number of patients)	Target	Median survival (months)	Outcomes			
				LR (%)	DBF (%)	LMD (%)	Symptomatic RN (%)
Asher, 2014 [28]	PreOP SRS (47)	GTV = PTV	NA	14.4 (1 yr)	38.2 (1 yr)	NA	NA
Patel, 2016 [29]	PreOP SRS (66) Vs. Postop SRS (114)	GTV = PTV PTV = cavity + 1–2 mm margin	17.1 13.5	15.9 (1 yr) 12.6 (1 yr)	32 (1 yr) 39.1(1 yr)	3.2 (1 yr) 3.2 (2 yr) 8.3 (1 yr) 16.6 (2 yr)	4.9 (2 yr) 16.4 (2 yr)
Patel, 2017 [44]	PreOP SRS (66) Vs. Postop WBRT [36]	GTV = PTV PTV = cavity + 1–2 mm margin	13.9 12.6	24.5 (2 yr) 25.1 (2 yr)	53.2 (2 yr) 45 (2 yr)	3.5 (2 yr) 9 (2 yr)	5.6 (2 yr) 0 (2 yr)
Prabhu, 2018 (Abstract only)	Pre-OP SRS (117)	GTV = PTV	17.2	19.9 (1 yr); 25.1 (2 yr)	45.3 (1 yr); 60.2 (2 yr)	4.3 (1 yr); 4.3 (2 yr)	2.6 (1 yr) 4.8 (2 yr)

In this prospective phase II trial, we will establish the efficacy of pre-operative SRS in local disease control. Since the tumor will be resected within 4 days of the delivery of the radiation, we will treat lesions up to 5 cm in size with SRS. In addition, there is no available published literature that describes early tumor cell molecular responses to radiosurgical doses of ionizing radiation in humans. We will simultaneously perform an exploratory analysis regarding histologic and molecular changes after radiosurgery for specimens removed to determine correlation between response to radiation at tumor margin and LC. This analysis will potentially provide molecular prognostic data for local and overall outcomes of patients with BMs.

### Study goals and objectives

#### Primary objective

To evaluate 6-month in-brain local control utilizing pre-operative SRS followed by surgical resection for up to 4 brain metastases.

#### Secondary objectives

Overall survivalProgression free survivalDistant-in-brain failureRate of leptomeningeal spreadRate of radiation necrosis.

#### Exploratory objectives

Molecular studies to investigate the relationship between radiation dose and DNA damage in tumor tissue. In addition, characterization of early histologic and molecular changes, in terms of gene expression, seen within the tumor following radiation.

## Methods/design

### Study design

This is a single-center, single-cohort, single-arm, prospective phase II trial to determine the local control at 6 months utilizing pre-operative SRS followed by surgery within 1–4 days of radiation treatment in neurologically symptomatic patients with up to 4 brain metastases.

### Study population

Patients with 1–4 metastatic lesions in the brain identified on a diagnostic brain MRI or CT with at least one meeting the criteria for surgical resection i.e. symptomatic or size > 3 cm, will be identified as potential study candidates. Amongst the study candidates, patients meeting the inclusion and exclusion criteria (Table 4) will be eligible to enroll in the study. Eligible patients who complete the Informed Consent Process will be registered in the OnCore® database and assigned a patient ID number for the clinical study.

**Table 4 Tab4:** Inclusion and Exclusion Criteria

Inclusion Criteria	
1. Radiographically confirmed solid tumor brain metastases 2. Criteria for surgical resection of at least one metastasis per neurosurgeon discretion 3. A diagnostic MRI Brain or CT Head demonstrating the presence of 1–4 solid tumor brain metastases and lesion to be resected no more than 5 cm in any direction, performed within 30 days prior to stereotactic radiosurgery. If multiple lesions are present, then the total brain metastases volume can be no more than 30 cm^3^ excluding the lesion to be resected. 4. For known primary, ds-GPA estimated median survival no less than 6 months 5. For unknown primary, GPA estimated median survival no less than 6 months 6. Surgical candidate per neurosurgeon discretion 7. Surgical resection able to be performed within 1–4 days after radiosurgery 8. Stereotactic radiosurgery candidate per radiation oncologist 9. ≥ 18 years old at the time of informed consent 10. Ability to provide written informed consent and HIPAA authorization 11. Platelet count > 100 k/ml, Hgb > 7.5 g/dL, INR < 1.3, ANC > 1.5 k/ml 12. Patients currently on cytotoxic chemotherapy or immunotherapy are eligible, not including anti-VEGF therapy	
Exclusion Criteria	
1. Patients who received anti-VEGF therapy within 6 weeks prior to enrollment 2. Major medical illnesses or psychiatric impairments, which in the investigator’s opinion will prevent administration or completion of the protocol therapy and/or interfere with follow-up 3. Patients with more than 4 brain metastases on MRI Brain or CT Head 4. Lesion to be resected is more than 5 cm 5. Total volume of metastatic disease more than 30 cm3 excluding lesion to be resected 6. Patients with leptomeningeal metastases documented by MRI or CSF evaluation 7. Previous whole brain radiation therapy 8. Previous radiation therapy to lesion to be resected 9. Planned adjuvant focal therapy including additional radiation therapy to the brain 10. Not a surgical candidate per neurosurgeon’s discretion 11. Not a radiosurgical candidate per radiation oncologist’s discretion 12. Surgery unable to be performed between 1 and 3 days after radiosurgery 13. Women who are pregnant or nursing are not eligible as treatment involves unforeseeable risks to the fetus or child 14. Patients who have a known primary and have an estimated median survival less than 6 months per ds-GPA 15. Patients who have an unknown primary and have an estimated median survival less than 6 months per GPA	

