### Surgical resection

At least one of the 4 lesions has to be either larger than 3 cm or symptomatic to meet the surgical resection criteria. One to four days after radiosurgery, the dominant lesion(s) will be maximally resected and labeled tissue will be sent to the neuropathology department for clinical diagnosis and radiobiological correlative studies. If for safety concern or other considerations, gross total resection is not reached, the residual disease in the setting of subtotal resection will be closely observed given that it has been treated with a definitive dose of SRS, reserving salvage local therapy for cases of progression. [29] Patients who received subtotal resection will be recorded and analyzed as well for risk stratification.

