### Response and progression assessment in neuro-oncology brain metastases (RANO-BM) [32]

Following delivery of SRS and surgical resection, all patients will be assessed for their clinical performance status (GPA/ds-GPA/ ECOG performance status/KPS) as well as toxicity at follow-up intervals as detailed in Table 6. Serial MRIs will be analyzed per RANO-BM criteria for assessment of LC, DBF and cranial progression free survival. [32] Initiation or continuation of chemotherapy, immunotherapy or other systemic agents is allowed per medical oncologist discretion.

**Table 6 Tab6:** Study Protocol and follow up timeline

	Screening (within 30 days of SRS)	Stereotactic radiosurgery	Surgery (1–4 days post SRS)	1 Month Follow Up^a^ (30 days post SRS)	Follow Up^b^ (every 3 m until 2 yrs)	Long Term Follow Up^c^ (> 2 yr. post SRS)
Radiation oncology consult	x					
Neurosurgical consult	x					
Medical History	x			x	x	x
Physical Examination	x			x	x	x
Vitals	x	x	x	x	x	x
ds-GPA/GPA/ECOG performance status/KPS	x			x	x	x
Diagnostic MRI Brain or CT Head	x					
MRI Brain Planning Scan^f^		x				
WBC, Hgb, platelets, INR, ANC^d^	x		x			
Urine pregnancy test	x					
Toxicity assessment				x	x	
MRI Brain^e^					x	x
Tissue collection			x			

^a^Variations of +/− 14 days from the scheduled visit are permitted

^b^Variations of +/− 30 days from the scheduled visit are permitted

^c^Subjects will be followed at physician’s discretion, approximately every 6 months after 2 years post SRS, per standard of care. Any MRI Brain, physical exam or vitals obtained at these appointments will gathered. However, if these procedures are not performed per standard of care, this will not be a deviation

^d^Repeating Hgb, platelets, INR and ANC at time of surgery is per discretion of neurosurgeon

^e^MRI Brain performed at Indiana University will have sequences including contrast, no contrast, FLAIR, DTI and PWI. If patient receives MRI Brain outside of Indiana University, a minimum of contrast, no contrast and FLAIR will need to be obtained and all sequences mentioned above are encouraged

^f^Variations of −30 days from the scheduled visit are permitted for linear accelerator based SRS, and may include the baseline screening MRI at the treating radiation oncologist’s discretion

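### Table 4 sets two surgical windows: a patient operable only on day 4 after radiosurgery meets inclusion criterion 7 and also exclusion criterion 12

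*Protocol article*

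**What the plan says.** Under Study population, the article states that "patients meeting the inclusion and exclusion criteria (Table 4) will be eligible to enroll in the study", so a candidate has to satisfy both lists. Inclusion criterion 7 reads "Surgical resection able to be performed within 1–4 days after radiosurgery". Exclusion criterion 12 reads "Surgery unable to be performed between 1 and 3 days after radiosurgery".

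Five places outside Table 4 also give a timing for surgery:

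- Abstract, Methods: "symptomatic lesions will be resected within 1–4 days after SRS"
- Background, last paragraph: "the tumor will be resected within 4 days of the delivery of the radiation"
- Study design: "pre-operative SRS followed by surgery within 1–4 days of radiation treatment"
- Surgical resection: "One to four days after radiosurgery, the dominant lesion(s) will be maximally resected"
- Table 6, column heading: "Surgery (1–4 days post SRS"

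The article does not explain the 3-day limit in exclusion 12, and it does not say which criterion governs when the two disagree.

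**The concern.** Eligibility criteria are applied as written. If two lines of one table give different answers for the same candidate, the outcome depends on which line the screener follows: the patient may be enrolled, refused, or enrolled and later logged as an eligibility violation. Read literally, exclusion 12 turns away a patient whom the rest of the article accepts.

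The interval between SRS and surgery is part of the regimen as the Study design section describes it, and it determines how long after irradiation the tissue for the correlative work is taken. The article reports that recruitment is under way, so the ambiguity may already have affected screening decisions. Any doubtful case is better classified before its local control outcome is known than after.

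**Working it through.** **Step 1: the windows side by side.**

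| Place in the article | Days after SRS |
|---|---|
| Abstract, Methods | 1–4 |
| Background | within 4 |
| Study design | 1–4 |
| Table 4, inclusion 7 | 1–4 |
| Table 4, exclusion 12 | 1–3 |
| Surgical resection | 1–4 |
| Table 6 | 1–4 |

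Six of the seven statements allow day 4. Exclusion 12 is the only one that does not.

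**Step 2: who is in conflict.** Let F be the set of days within 1–4 on which a patient could be operated on.

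- Inclusion 7 is met if F contains at least one of days 1, 2, 3, 4.
- Exclusion 12 is triggered if F contains none of days 1, 2, 3.

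There are 2^4 − 1 = 15 non-empty sets F. Both conditions hold for exactly one of them, F = {4}. Any patient with a feasible day among 1, 2 or 3 passes both criteria, whichever day surgery finally takes place. A patient with no feasible day in 1–4 fails both criteria, so the two lines agree.

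**Step 3: whether the sample size calculation is touched.** Inputs from Statistical analysis: n = 44, null proportion 0.83, alternative 0.95, one-sided alpha 0.05, binomial test. With X the number of patients with local control, the cut-off is the smallest r for which P(X ≥ r | n, 0.83) ≤ 0.05, and power is P(X ≥ r | n, 0.95).

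| n | r | Failures allowed | Actual alpha | Power |
|---|---|---|---|---|
| 44 | 41 | 3 | 0.0450 | 0.823 |
| 43 | 41 | 2 | 0.016 | 0.635 |
| 42 | 40 | 2 | 0.018 | 0.649 |
| 40 | 38 | 2 | 0.024 | 0.677 |
| 36 | 34 | 2 | 0.043 | 0.732 |

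The first row reproduces the stated 82%. Neither eligibility line enters this calculation. The lower rows show what an unreplaced loss from the 44 would do, whatever its cause; they bear on the stronger reading taken up below.

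**The case against.** The strongest reply is that exclusion 12 is a slip. Six statements allow day 4, the article condenses a fuller protocol that is not shown, and the treatment window described outside Table 4 is consistent. That may well explain how the line arose. It does not remove the line, which is a complete sentence in the current eligibility table and excludes patients for as long as it stands.

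Three objections to the size of the point do stand.

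- **Scope.** A reader might infer that every patient scheduled for, or operated on, day 4 is affected. The wording does not support this: both criteria ask whether surgery can be done, not when it was done.
- **Power.** A reader might infer from the table above that each affected patient costs the trial power, with 82% falling to 64% at 43 patients. The arithmetic is right but the inference is not. The Statistical analysis section defines no per-protocol or eligible-patient denominator for the primary test. A candidate refused at screening never enters the 44, so recruitment simply continues to 44. The drop from 44 to 43 also reflects the discreteness of the binomial test: permitted failures go from 3 to 2 and actual alpha from 0.045 to 0.016. Power then rises again, to 0.649 at 42 and 0.732 at 36. Loss of one patient for any reason would do the same, so the figure does not measure the harm of this wording.
- **Bias.** The primary endpoint and its test do not depend on day 3 versus day 4. The molecular work is exploratory, and the article describes no analysis by SRS-to-surgery interval.

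**Conclusion.** The contradiction is real and lies in binding eligibility rules. Inclusion 7 and exclusion 12 cannot both be applied to a patient whose only feasible surgical day is day 4, and exclusion 12 also disagrees with five other places in the article. Its reach is limited to that one group, whose number cannot be learned from the article and may be small or zero.

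The consequence is inconsistent enrolment and an unclear eligible population. No statistical figure is wrong on this account, and the 82% power is unaffected. The point deserves correction because a rule followed as written excludes patients the design accepts, but there is no statistical ground for ranking it among the most serious faults.

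The conclusion rests on two readings: that both lists in Table 4 must be satisfied, as the text says, and that both criteria concern ability to operate, as their wording says. Which window is clinically appropriate is not judged here.

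**What to change.** Reconcile exclusion criterion 12 with inclusion criterion 7, the abstract, the background, the study design, the surgical section and Table 6, so that one window appears everywhere. The investigators decide which.

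Check the screening log for patients operable only on day 4, whether enrolled or refused, and record the eligibility status of each before outcomes are analysed. Patients who could have been operated on earlier but whose surgery took place on day 4 need no reclassification under these two criteria as now worded.

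The cost is a minor protocol amendment and a log check. The sample size and the primary test stay as they are.
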